## Abstract

**Background:**

Pre-eclampsia (PE) is a multiorgan disorder that affects 2–5% of all pregnant women. Present recommendations for when to start aspirin in high-risk women are after 11 wk of gestation.

**Objective:**

We present a protocol to investigate the effectiveness of aspirin use from early pregnancy, which is a randomized controlled trial to assess whether prescribed low-dose aspirin from early pregnancy reduces the prevalence of early and late-onset PE. Additionally, to compare the effectiveness of aspirin administration before and after 11 wk in reducing the occurrence of PE?

**Materials and Methods:**

All pregnancies at risk of PE, according to demographic and midwifery history, who are referred to the Maternal-Fetal Clinic of Tehran University hospital, Tehran, Iran were invited to take part in the trial. The outcomes of pregnancy and newborns will be gathered and analyzed. The first registration for the pilot study was in January 2023, and the participants were recognized as high-risk for PE. In addition, enrollment in the main study will begin as of October 2023.

## 1. Introduction

Pre-eclampsia (PE) is a multiorgan disorder that occurs in 2–5% of pregnancies (1). The cytotrophoblasts infiltrate into the decidual portion of spiral arteries, but they do not reach the myometrial portion. This results in the vessels remaining narrow (2).

A study has shown that there is a positive feedback loop between endothelial dysfunction and oxidative stress in the placenta in PE caused by sFlt-1. The study found that this positive feedback loop activates the apoptosis pathway in trophoblasts in preeclamptic placentas. Additionally, it was discovered that low-dose aspirin (LDA) can alleviate oxidative stress and endothelial dysfunction mediated by sFlt-1 and inhibit apoptosis of trophoblasts in PE (3).

PE is associated with turnover and increased platelet-derived thromboxane levels. These findings have led to randomized controlled trials (RCT) examining LDA therapy at a dose of 150 mg in pregnancies at risk of the disease (4, 5).

In the ASPRE trial the aspirin for evidence-based PE, participants were randomized to take aspirin or a placebo in 11–14 wk. The authors concluded that LDA significantly reduces the rate of preterm PE (6). An RCT examined the effects and safety of LDA (81 mg/day) starting at 6 wk and 13
${\;}^{6/7}$
 wk in nulliparous women, in low and middle-income countries. They reported significant reductions in perinatal mortality, fetal loss, early preterm labor (PTL), and the incidence of hypertensive disorders (7). Meta-analyses suggest that taking LDA starting at or before 16 wk of pregnancy significantly reduces the risk of severe PE and other placenta-related complications (8).

The mechanism of LDA remains vague, but it could include a recovery of the remodelling of spiral arteries, and increase the uterine artery blood flow related to the improved transformation of spiral arteries (5).

Another study found that aspirin's effect on sFLT1 production from cytotrophoblasts is replicated through cytochrome c oxidase I inhibition but not COX2 inhibition (9).

Panagodage and colleagues hypothesized that LDA improves trophoblast function affected by PE by altering cytokine production and secretion, including placental growth factor, resulting in an overall positive effect on trophoblast cell function in vitro (10).

The safety of using LDA during pregnancy has been extensively studied and no significant adverse maternal or fetal/neonatal effects have been reported (8, 11).

The results of a RCT on the safety of using LDA during pregnancy show different findings from previous observational studies on aspirin use during the first trimester. The previous studies suggested an increased risk of certain birth defects such as gastroschisis, cryptorchidism, oral clefts, neural tube defects, microphthalmia, and limb body wall defects. However, the RCT findings are similar to other large studies that reported no association between aspirin use and birth defects overall. Additionally, no links between LDA and malformations have been reported. This could be due to the fact that LDA is broken down in the mother's liver, resulting in low fetal exposure (12).

No original RCT has been conducted on the effectiveness of LDA administration from early pregnancy vs. after 11 wk for the prevention of PE.

### Primary objective

To determine the effectiveness of early use of LDA in high-risk pregnancies in reducing the incidence of early and late-onset PE.

### Secondary objectives

 
 To determine the effect of LDA prescription during early pregnancy on adverse perinatal outcomes:

 
 Incidence of placental abruption (clinically or on placental examination)

 
 Incidence of small for gestational age (SGA) (
<
 5
${\;}^{\text{th}}$
 centile) requiring delivery at 
<
 34 wk and 
<
 37 wk

 
 Incidence of stillbirth or intrauterine fetal death (IUFD) at 
≥
 20 wk

 
 Incidence of spontaneous preterm delivery at 
<
 34 wk and 
<
 37 wk

 
 To determine the effect of LDA during early pregnancy on neonatal mortality and morbidity:

 
 Respiratory distress syndrome is described as the requirement for surfactant and ventilation due to prematurity

 
 Ventilation requirement is defined as the need for positive pressure

 
 Admission to neonatal intensive care unit (NICU)

## 2. Materials and Methods

### Trial design

The study has 2 portions: a pilot study with quality control of the study, and a parallel assessor-blind randomized trial (main RCT) by allocation ratio 1:1. According to the Gantt table, the study schedule is set out (Table I).

### Pilot study and quality control of the study

A pilot study is used before the start of the main RCT to assess the feasibility of recruitment and the ability of the center to conduct the RCT.

A total of 1686 pregnancies were screened and 200 high-risk women with PE were enrolled in the pilot study. The complications of the main RCT include the need to conduct periodical targeted monitoring during the study for quality control of the recruitment of participants, as well as the correct measurement of the uterine arteries pulsatility index (UtA-PI), biochemical screening tests, the appropriate follow-up of the participants, monitoring, the correct use of the medicine, and the evaluation of the quality of the data collection. Additionally, if necessary, we will implement strategies to improve study quality such as retraining (including health staff involved in the follow-up of the participants and UtA-PI measurement). Accordingly, the ability of the center and the study team to conduct this pilot trial has been evaluated and was successful. Recruitment for the pilot study was started in January 2023. The pilot study data will be analyzed and published.

**Table 1 T1:** Gantt table (study schedule chart)

**Time point****		**Enrolment**	**Allocation**			**Close-out**
		**10.01.2023**	**01.02.2023**	**01.03.2023**	**etc.**	**30.12.2023**
**Enrolment**				
**Eligibility screen**				
**Informed consent **				
**Allocation**				
**Interventions**					
**Assessments**				
	**List baseline variables**				
	**List outcome variables**				

### Participants

The participants are pregnant women who are at risk of PE based on their demographic characteristics and obstetrics history, according to the ACOG, USPST, and SMFM guidelines. During a structured clinical interview, all enrolled participants will be evaluated using a questionnaire designed by the perinatology fellowship senior based on the guidelines mentioned. All participants were involved in the research setting. Additionally, patients and their families were central to disseminating the baseline information to motivate community involvement during and beyond the study.

#### Inclusion criteria

I. No serious maternal illness or learning difficulties

II. Pregnancies at risk of PE conforming to the USPSTF (13), ACOG, and SMFM (14) guideline criteria:

If there are one or more of the following criteria (major criteria), participants are considered at high risk:

1) Prior pregnancy with PE particularly early-onset PE or with an adverse outcome

2) Chronic hypertension

3) Type 1 or 2 diabetes mellitus

4) Renal disease

5) Autoimmune disease (antiphospholipid syndrome, systemic lupus erythematosus)

6) Multifetal gestation

If there are 2 or more of the following criteria (moderate criteria), they are considered high-risk:

1) Nulliparity

2) Obesity (body mass index 
>
 30 kg/m^2^)

3) Age 
≥
 35 yr

4) Family history of PE in mother or sister

5) Obstetric risk factors (such as a history of low birth weight or SGA, and other adverse pregnancy outcomes, 
>
 10 yr pregnancy interval)

6) Low socioeconomic level

7) In vitro fertilization (IVF)

#### Exclusion criteria

1) Hypersensitivity to nonsteroidal anti-inflammatory drug products

2) Asthma, rhinitis, and nasal polyps

3) Severe renal or severe hepatic impairment

4) History of gastrointestinal bleeding or active peptic ulcer disease

5) Vaginal bleeding or significant hematoma on ultrasound

6) Gestational age 
>
 16 wk

### Sample size

The sample size estimation of the main RCT was based on data from the ASPRE trial (6). The results of this trial showed that preterm PE occurred in 1.6% of the intervention group as compared with 4.3% in the placebo group. We calculated that the enrollment of 1792 participants in a 1:1 ratio of distribution (896 participants in each group) would provide the trial with a power of 90% (alpha level of 5%). If we are allowed a 10% loss to follow-up, the sample size will reach 986 participants in each group. A total of 1972 eligible participants will be randomly selected to participate in the trial arms. Furthermore, we proposed a sample size of 200 high-risk pregnancies in the pilot study and quality control. By screening 1686 pregnant women who attended the Maternal-Fetal hospital Clinic, we achieved this sample size. From January 2023, after obtaining written conscious consent, the trial began with 100 participants in each group at a 1:1 ratio, randomly.

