### Intervention

After the participant screening, written informed consent was obtained from them, which was approved by the Tehran University Ethics Committee, Tehran, Iran.

During the first visit, vital signs, including blood pressure, weight, and height for accounting for body mass index, were measured. A complete record of medication usage is obtained, particularly those that interact with aspirin, such as anticoagulants, antiplatelet agents such as clopidogrel, antidepressants, and corticosteroids, smoking, and alcohol consumption. 30 days after aspirin was administered, a follow-up telephone interview was conducted for side effects and adverse events. At each clinical visit, PE symptoms and the presence of edema were noted and recorded. In addition, participants were asked about the possible side effects of aspirin.

In the pilot study, 200 eligible participants were randomly selected (100 participants in each group). Individuals who received LDA before 11 wk of gestation (optimally from the detection of the fetal heartbeat by ultrasound exam) were considered the intervention group and those who receive LDA after 11 wk are the control group. In the control group, the cut-off gestational age to prescribe aspirin was 16 wk. In both groups, the initial dose of aspirin is 80 mg per day, and it will be continued until 36 wk or in the case of premature delivery.

The mean UtA-PI is measured simultaneously with nuchal translucency (NT) determined through a transabdominal ultrasound exam at 11–13
${\;}^{6/7}$
 wk. In addition, a combined aneuploidy screening test was requested by measuring the maternal serum-free beta-human chorionic gonadotropin (β-hCG) and pregnancy-associated plasma protein-A (PAPP-A) using the Cobas-E-411 analyzer.

If there are any criteria, the initial dose of aspirin (80 mg) is changed to 150 mg per day:

•
 PAPP-A 
<
 0.4 in the first trimester (15)

•
 PE risk greater than or equal to 1/100 in the aneuploidy screening test (16)

•
 High resistance of uterine arteries in color Doppler ultrasound (the mean UTA-PI 
>
 95
${\;}^{\text{th}}$
 percentile or bilateral notching) (17)

At 18–22 wk, the mean UtA-PI will be measured and recorded at the same time as the anomaly scan. Ultrasound examinations are performed by 2 trained prenatal fellowships that have Fetal Medicine Foundation certification.

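### The 90% power rests on an aspirin-versus-placebo difference in preterm pre-eclampsia and is unsupported for a comparison of earlier with later aspirin on a different outcome

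*Protocol article*

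**What the plan says.** The Sample size section takes its event rates from the ASPRE trial, where "preterm PE occurred in 1.6% of the intervention group as compared with 4.3% in the placebo group". From these it derives 896 women per arm (1792 in total) at 90% power and a 5% alpha level. It then adds an allowance: "If we are allowed a 10% loss to follow-up, the sample size will reach 986 participants in each group".

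The Introduction describes the source trial as one in which "participants were randomized to take aspirin or a placebo in 11–14 wk".

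The Intervention section of this trial puts women who start aspirin before 11 weeks in the intervention group, while "those who receive LDA after 11 wk are the control group", with 16 weeks as the latest start. It adds: "In both groups, the initial dose of aspirin is 80 mg per day". The arm definitions follow a sentence about the pilot, but the Objective in the abstract, the Discussion and the Strengths and limitations section give the same contrast of early start with start after 11 weeks for the trial as a whole.

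The Primary outcome section names early-onset (before 34 weeks) and late-onset (34 weeks or later) PE.

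**The concern.** The assumed difference of 2.7 percentage points is the effect of giving aspirin rather than placebo. This trial has no placebo or untreated arm. What it can estimate is the added effect of starting aspirin earlier in women who would all receive it anyway. Nothing in the protocol justifies a 2.7-point difference for timing alone. The rates also refer to preterm PE, which is not the primary outcome.

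What is at stake is how the result will be read. A reader told that the trial has 90% power is likely to take a non-significant difference as evidence that starting before 11 weeks adds nothing. The stated calculation does not support that reading.

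**Working it through.** **Inputs.** p1 = 0.043, p2 = 0.016, alpha 5%, power 90%, 896 per arm, 10% loss and 986 per arm, all from the Sample size section. That section does not state sidedness or formula. I take the test as two-sided because that reproduces the stated number.

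**Step 1: reproduce 896.** Mean rate 0.0295.

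n0 = [1.960·√(2·0.0295·0.9705) + 1.2816·√(0.043·0.957 + 0.016·0.984)]² / 0.027²
= [1.960·0.23929 + 1.2816·0.23853]² / 0.000729 = 823.2

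With continuity correction: n = (n0/4)·[1 + √(1 + 4/(n0·0.027))]² = (823.2/4)·(1 + 1.0863)² = 895.8, that is 896.

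The match is exact, so the aspirin-versus-placebo rates were used without adjustment. Other variants do not match: 824 two-sided without correction, 671 one-sided, 744 one-sided with correction.

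**Step 2: compare what was sized with what is tested.**

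| | Source trial, used for sizing | This trial |
|---|---|---|
| Contrast | aspirin vs placebo | aspirin before 11 wk vs aspirin after 11 wk |
| Outcome | preterm PE | early-onset and late-onset PE |
| Start of aspirin | 11–14 wk | before 11 wk; controls after 11 wk, up to 16 wk |

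**Step 3: power at 896 per arm under stated scenarios.** The protocol gives neither the control rate nor the effect, so these are assumptions.

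Power = Φ{[|pC − pE| − 1.960·√(2·p̄(1−p̄)/n)] / √[(pC(1−pC) + pE(1−pE))/n]}; the corrected version subtracts a further 1/n from |pC − pE|.

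Example, 1.6% vs 0.8%: (0.008 − 1.960·0.005144)/0.005141 = −0.405, and Φ(−0.405) = 34%.

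| Control rate | RR | Early-start rate | Power | Power with correction |
|---|---|---|---|---|
| 1.6% (preterm PE, source aspirin arm) | 0.37 | 0.6% | 53% | 44% |
| 1.6% | 0.5 | 0.8% | 34% | 27% |
| 1.6% | 0.7 | 1.12% | 14% | 10% |
| 4.3% (preterm PE, source placebo arm) | 0.5 | 2.15% | 73% | 69% |
| 4.3% | 0.7 | 3.01% | 31% | 26% |
| 10% (assumed, any PE) | 0.5 | 5% | 98% | 98% |
| 10% | 0.6 | 6% | 88% | 86% |
| 10% | 0.7 | 7% | 62% | 59% |

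RR 0.37 is 1.6/4.3, the whole aspirin-versus-placebo effect repeated on top of aspirin. Without correction, 90% power at 896 per arm needs an RR of about 0.105 at a 1.6% control rate, 0.39 at 4.3% and 0.59 at 10%.

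**Step 4: loss allowance.** 896 × 1.1 = 985.6, the stated 986. Keeping 896 after 10% loss needs 896/0.9 = 995.6, so 996. With 986, 986 × 0.9 = 887 remain. On the plan's own rates, 887 instead of 896 gives 89.7% instead of 90.0% power with correction (92.0% instead of 92.2% without). Every figure in the table falls by less than half a point.

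**The case against.** The strongest reply is that low power has not been shown either. The primary outcome covers early- and late-onset PE, which together include term disease, and women are selected for prior PE, chronic hypertension, diabetes, multifetal pregnancy and similar risks. The control rate for that outcome could be well above any preterm-PE rate. At an assumed 10%, 896 per arm has 88% power at RR 0.6 and 98% at RR 0.5. This stands, with two limits. The protocol states neither such a rate nor such an effect. And if early-onset PE were tested on its own, its rate could be lower instead.

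Two stronger readings are therefore tempting but not supported. A reader might infer that 1.6% is the control rate on the plan's own figures. The protocol does not say so: the source trial started aspirin at 11–14 weeks, controls here may start as late as 16 weeks, and equivalence of the two regimens and populations is not established. A reader might also take 4.3% as a ceiling on the control rate, and conclude that the trial cannot detect any plausible benefit. But 4.3% is a preterm-PE rate in another population and does not bound the rate of all PE here.

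It could also be said that power assumptions belong in an analysis plan. That does not help here, because the protocol itself states the inputs and the 90%.

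**Conclusion.** The 90% power claim is wrong as written for this trial's comparison. The 896 is computed correctly, but for another contrast (aspirin versus placebo) and another outcome (preterm PE). This is a wrong design assumption and not an arithmetic slip.

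True power cannot be fixed from the protocol. Across the uncorrected scenarios it runs from 14% to 98%, depending on a control rate and an added effect that are not given. The 53%, 34% and 14% figures depend on taking 1.6% as the control rate and preterm PE as the outcome. They show how far the 90% can fail and are not an estimate of the trial's power.

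The loss allowance is a real but minor error: 10 women per arm (996 − 986), about 0.3 points of power on the plan's own inputs.

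**What to change.** In the Sample size section:

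- Withdraw the 90% claim and say that the source trial's rates describe aspirin versus placebo for preterm PE.
- State power and the smallest detectable reduction for earlier versus later start, on the outcome named in the Primary outcome section, over a justified range of event rates in women starting aspirin after 11 weeks. The range should not be confined to 1.6–4.3%, which are preterm-PE rates.
- Calculate these at the evaluable number per arm, about 887 after 10% loss from 986, and name the sidedness and formula.
- Correct the loss allowance: either 996 per arm to retain 896, or a statement that 986 leaves about 887.

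In the Statistical analysis section, commit to reporting a non-significant primary result with its confidence interval and not as absence of added benefit.

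The cost is a rewritten paragraph and probably a less favourable stated power. The restatement needs no extra patients; only the choice of 996 would add 10 per arm.

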During the trial, some participants may be excluded from the study due to reasons such as abortion or IUFD below 20 wk of gestation or major fetal abnormalities or side effects of aspirin or discontinue the intervention. We will use the CONSORT checklist when writing our report.

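### The 10% loss allowance is applied by multiplying by 1.10 rather than dividing by 0.90, so 986 per arm covers a 9.1% loss; the effect on power is small

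*Protocol article*

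**What the plan says.** The Sample size section takes its event rates from an earlier placebo-controlled trial, in which "preterm PE occurred in 1.6% of the intervention group as compared with 4.3% in the placebo group". With a 5% alpha level and 90% power it arrives at "the enrollment of 1792 participants in a 1:1 ratio of distribution (896 participants in each group"). It then adds an allowance: "If we are allowed a 10% loss to follow-up, the sample size will reach 986 participants in each group", and gives a total of 1972.

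Other sections provide for taking women out after randomisation. The Intervention section lists "abortion or IUFD below 20 wk of gestation or major fetal abnormalities or side effects of aspirin or discontinue the intervention" as reasons for exclusion during the trial. The sections on gathering side effects, Monitoring and Safety considerations remove from the final analysis women who stop the drug permanently, who have severe side effects that require stopping, or who have an adverse effect that a physician attributes to aspirin. None of these sections gives an expected rate, and the Sample size section does not mention them.

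**The concern.** A loss allowance is meant to leave the required number of analysable participants once the assumed fraction of those randomised is gone. Adding 10% of the required number is not the same as allowing for 10% of the randomised number to be lost, and the first always falls short of the second. The stated 896, 10% and 986 therefore cannot all hold.

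The scope of the allowance is also unclear. It is described only as loss to follow-up, while the protocol has its own rules for leaving followed women out of the analysis. If those removals were additional to the 10%, the analysed number would be lower again. At stake are the stated number of analysable women and the power attached to it.

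**Working it through.** **Inputs, all from the Sample size section:** p1 = 0.016, p2 = 0.043, so d = 0.027 and the mean rate is p̄ = 0.0295; alpha 5% (sidedness not stated; two-sided reproduces the figure); power 90%; ratio 1:1; loss 10%.

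**Step 1: reproduce 896.** Without continuity correction:

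n = [1.960·√(2p̄(1−p̄)) + 1.2816·√(p1(1−p1) + p2(1−p2))]² / d²
= [1.960·√0.05726 + 1.2816·√0.05690]² / 0.000729 ≈ 823.2, so 824.

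With continuity correction:

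n' = (n/4)·[1 + √(1 + 4/(n·d))]² = (823.2/4)·[1 + √(1 + 4/22.23)]² ≈ 895.8, so **896**.

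This matches the plan exactly. The other variants tried do not: unpooled variance 821, arcsine 781, one-sided 671 (744 with correction). The base figure is sound and, on its own method, carries no spare margin.

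**Step 2: reproduce 986.** 896 × 1.10 = 985.6, so **986** per arm and 2 × 986 = 1972 in total. Both stated figures match.

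**Step 3: the figure that a 10% loss requires.** 896 / (1 − 0.10) = 995.6, so **996** per arm and 1992 in total. The difference is 10 per arm, 20 overall, about 1%.

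**Step 4: what 986 delivers.** 986 × 0.90 = 887.4, so **887** per arm, 9 below 896. The loss at which exactly 896 remain is 1 − 896/986 = **9.1%**.

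**Step 5: power.** Two-sided 5%, with the plan's own rates:

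power = Φ{[d − c − 1.960·√(2p̄(1−p̄)/n)] / √([p1(1−p1) + p2(1−p2)]/n)}, where c = 1/n with the correction and c = 0 without it.

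| Attrition from 986 | n per arm left | Power, corrected | Power, uncorrected | Randomised per arm to keep 896 |
|---|---|---|---|---|
| 9.1% | 896 | 90.0% | 92.2% | 986 |
| 10% | 887 | 89.7% | 92.0% | 996 |
| 15% (assumption) | 838 | 87.8% | 90.5% | 1055 |
| 20% (assumption) | 789 | 85.6% | 88.7% | 1120 |

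Only the 10% row rests on a loss rate that the protocol states. The 15% and 20% rows are illustrations, because no removal rate is given.

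**The case against.** The strongest reply is that the slip does not matter in practice. The two targets differ by 1%, and corrected power falls by about 0.3 points, which still rounds to 90%. The Statistical analysis section names the Chi-square test for categorical data and mentions no continuity correction. Without one, 824 per arm suffice, 986 keeps at least 90% power up to 1 − 824/986 = 16.4% attrition, and only the 20% illustration falls short. That stands as to consequence. It does not make 986 the right figure for a 10% loss, and 896 itself is reproduced only with the correction, so the corrected powers are a fair reading of the plan's own method.

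A reader might go further and infer that the removals after randomisation come on top of the 10%, so that the trial is materially underpowered. The documents do not support this. The Sample size section does not say whether its 10% covers those women, and in a condensed article the term may have been used loosely for everyone not analysed. With no removal rate given, no shortfall beyond the 10% row can be derived. What remains is an ambiguity to be cleared up.

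**Conclusion.** The inflation step is wrong as written. At the stated 10% loss, 986 per arm leaves 887, not 896; the figure that matches a 10% loss is 996 per arm (1992 in total), and 986 matches a 9.1% loss. This is certain from the section's own numbers.

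It is a minor correction: about 0.3 points of power with the continuity correction, and power still at 92.0% without it. These powers assume a two-sided 5% test and the planning rates of 1.6% and 4.3%. The scope of the allowance is undefined with respect to the removal rules elsewhere in the protocol. Whether that costs any power cannot be judged from the document.

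**What to change.** Correct the sentence in the Sample size section in one of two ways.

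- Keep the planned numbers: *986 per arm (1972 in total) allows for 9.1% attrition; at 10% attrition 887 per arm remain, with power of about 89.7%.*
- Keep the 10% allowance: give 996 per arm (1992 in total).

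In either case, add that attrition here counts all randomised women not in the primary analysis for any reason. Defining it by a missing outcome would not be enough, because a woman who stops aspirin may have a recorded outcome and still be removed by rule. If power at higher attrition is quoted, label the attrition rate as an assumption and say whether the continuity correction is used.

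The first option needs only a change of wording and no extra recruitment; a stated figure becomes slightly less favourable. The second adds 20 women. Neither addresses the bias that removing randomised women can cause, which a larger sample does not cure and which is a separate matter.
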